## Figures and Tables

**Figure 1 ijerph-17-06569-f001:**
[figure not shown]
Schematic of the Food Intake REstriction for Health OUtcome Support and Education (FIREHOUSE) trial subject selection, illustrating study cohort World Trade Center-lung injury (WTC-LI) as a subset of the larger World Trade Center-Health Program (WTC-HP) enrolled Fire Department of New York (FDNY) first responders. WTC-HP, World Trade Center health program; SGRQ, St. George’s Respiratory Questionnaire; CAT, Computerized Axial Tomography; SF-36, 36-Item Short Form Survey Instrument; 6MWT, Six Minute Walk Test; FeNO, fractional nitric oxide (NO) concentration in exhaled breath.

**Figure 2 ijerph-17-06569-f002:**
[figure not shown]
Study design of FIREHOUSE Trial. All participants will be enrolled during the enrollment period at Visit 0. At Visit 1, cohort will complete the dietary assessment/food frequency questionnaire, receive routine medical care, and obtain baseline measurements. Randomization will then occur and groups will be assigned to either LoCalMed or Usual Care groups. LoCalMed Dietary and Intervention group will receive weekly or biweekly technology-driven nutrition visits as scheduled, whereas Usual Care group will receive quarterly flyers to perform routine medical care. Follow-up measurements at Visit 2 will be collected at the end of the 6-month intervention for both groups. The World Trade Center-Health Program (WTC-HP) will be available throughout the time period to all participants to provide other medical care.

**Table 1 ijerph-17-06569-t001:** Inclusion and exclusion criteria for the randomized controlled clinical trial (RCT) FIREHOUSE Study.

Inclusion Criteria	Exclusion Criteria
Male sex, over age 21 years at enrollment	Pre-existing conditions including (and not necessarily limited to) active cancer, severe heart disease, significant cognitive impairment, eating disorders, significant psychiatric illness, end-stage COPD, severe pulmonary HTN, or organ transplant
FDNY rescue and recovery worker	Concomitant use of interfering medication(s) or devices within one month prior to enrollment
Documented WTC exposure	Severe GI illness that would prevent diet adherence
Enrolled in the FDNY WTC health program	Severe kidney disease requiring dialysis
Willing and able to consent for themselves to study enrollment	Severe liver disease requiring frequent medical intervention
Willing and able to participate in study procedures, to modify their diet and activity level	Participation in other diet modification studies
Able to perform ADLs independently	High-dose steroid (>20 mg prednisone or equivalent) or other hormonal treatments or chemotherapy within one month
Light duty or retired FDNY firefighters	Life expectancy < 6-months
FEV_1_ less than LLN of predicted at any time post 9/11	Recent significant weight loss > five percent TBW within one month
Spirometry within the last 36- months, and at post-9/11 visit	Significant alcohol use
BMI > 27 kg/m^2^ and < 50 kg/m^2^	
Able to demonstrate minimal proficiency using a smart phone	
Have means to accommodate transportation to/from in-person visits	

ADL, activities of daily living; HTN, hypertension; FDNY, Fire Department of New York; WTC, World Trade Center GI, gastrointestinal; TBW, total body weight; FEV_1_, forced expiratory volume in 1 s; LLN, lower limit of normal; BMI, body mass index; COPD, chronic obstructive pulmonary disease. Table 1 includes descriptions of both the inclusion and exclusion criteria that we will use to qualify potential study participants.

**Table 2 ijerph-17-06569-t002:** Schedule of enrollment, intervention, and assessment.

	Enrollment	Pre-Randomization Baseline	Post-Randomization		Close-Out
TIMEPOINT (Visit)	0	1	T/N	2	F/U
ENROLLMENT					
Eligibility screen	x				
Informed consent	x				
INTERVENTIONS					
LoCalMed			x	x	
Usual Care				x	
ASSESSMENTS					
Physical exam		x		x	
Phlebotomy		x		x	
EKG/PWV					
FeNO		x		x	
Spirometry		x		x	
Genome		x		x	
Microbiome					
Questionnaires		x		x	x
INSTRUCTIVE COMPONENTS					
Technology training			x	x	
Nutrition consultation			x	x	

PWV, pulse wave velocity; FeNO, fractional nitric oxide (NO) concentration in exhaled breath; T/N, technology and nutrition visit. Table 2 outlines the schedule we will follow during the study pertaining important benchmarks of enrollment, baseline visit (done pre-randomization), post visit (done after randomization), and closing out, or placing the participant off-study. The table is arranged according to the type of data collected (enrollment, interventions, assessments, instructive components). All follow-up components will be available to both intervention groups.

**Table 3 ijerph-17-06569-t003:** Intervention Behavioral Component Content.

Week	Education Materials (Videos)	Social Cognitive Theory (Coaching)
1	Introduction to the FIREHOUSE study.	Goals for life.
2	Self-monitoring of diet and physical activity—making sense of the numbers.	Where am I? Establishing the relevance of behavior change.
3	Being a Calorie Detective. Portion control and empty calories.	Setting goals.
4	Introducing physical activity into your life. Finding time for fitness. Exercise safety.	Self-Reward. Turning goals into habits.
6	Being a Fat Detective. Healthy and unhealthy fats, the contribution of fat to total calorie intake.	Social support. Developing and working your social support network.
8	Building duration and intensity of aerobic exercise.	Problem solving: Barriers and setbacks. Introduction to the problem-solving model.
10	Changing seasons, special occasions, life events, and eating at restaurants.	Problem solving: Behavioral triggers and stimulus control.
12	The role of sleep and stress in weight gain and loss.	Problem solving: Stress management.
14	Adding color and fiber to your diet.	Problem solving: Emotional eating.
16	The role of breakfast and meal frequency in weight loss success.	Problem solving: Eliminating negative self-talk.
18	Snacking and sugar-sweetened beverages. Empty calories.	Problem solving: Food cravings, addictions, and habitual over-eating.
20	Building muscles with strength training.	Problem solving: Anticipating high-risk situations.
22	Weight loss plateaus.	Problem solving: Lapse and relapse.
24	Putting it all together; review of lifestyle recommendations.	Problem solving: Coping with lapses and setting new goals.

Table 3 provides a breakdown of the schedule and learning goals for the intervention group. This is organized by the week in the study, as well as the title of the lesson and the social cognitive theory aiming to be achieved. During the first month, the LoCalMed study group subjects receive weekly education and coaching remotely, which changes to bi-weekly in remaining months 2–6.

**Table 4 ijerph-17-06569-t004:** Endpoints of the FIREHOUSE Trial.

	Outcome Measure	Description
**Primary Endpoint**	Body mass index (BMI) in kg/m^2^	Body mass divided by square of individual’s heights, with attempt to quantify and standardize amount of tissue mass across persons
**Secondary Endpoints**	FEV_1_	Usual spirometric technique with reproducibility and acceptability based on ATS/ERS guidelines. Allows best correlation with symptoms and pulmonary function
	Bioelectrical impedance analysis	InBody270 BIA scale. Measure lean body mass and total body fat percentage
	St. George’s Respiratory Questionnaire	Standardized/validated airways disease-specific survey to assess symptoms, activity hindrance, and overall impact
	Short Form 36	Standardized/validated general health survey to assess mental, emotional, and functional health status
	Pulse wave velocity	SphygmoCor (Atcor Medical) by carotid–femoral pulse discretion to measure vascular stiffness
	FeNO	NIOX VERO portable, to assess airway inflammation
	Vital Signs	BP, HR, RR, body temp, neck/waist/hip circumferences
	Electrocardiogram	Standard 12-lead ECG to assess axis changes
	Phlebotomy	Routine cell counts, metabolic panels, lipid panel. Possible further analysis of metabolomic fingerprints
**Exploratory Endpoints**	Microbiome	GenoTek Oragene-Gut personal stool collection kit
	Genome	DNA GenoTek Oragene-Discover saliva collection kit

FEV_1_, forced expiratory volume in one second; ATS/ERS, American Thoracic Society/European Respiratory Society; BIA, bio-electrical impedance analysis; BMI, body mass index; FeNO, fractionated exhaled nitrous oxide; ECG, electrocardiogram; BP, blood pressure; HR, heart rate; RR, respiratory rate. Table 4 details the primary, secondary, and exploratory endpoints of the study. Along with each endpoint is a description of what that measurement consists of.

**Table 5 ijerph-17-06569-t005:** Interim Monitoring Bounds.

Interim Analysis	Completion of Subjects/Group	Critical Value Z ±	*p* Value
1	30	3.951	0.000
2	50	2.686	0.007
3	70	2.129	0.033

Interpolated boundaries with 3-look O’Brien Fleming stopping boundaries 140 subjects randomized with 2-sided α = 0.036, power = 80%. Table 5 describes the statistical measures which will be the basis for our interim analysis.

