#### Sample Size and Interim Analysis

The primary objective is to compare the change in BMI in the two groups from pre-intervention to post-intervention after six months (intervention completion). The analysis for this primary objective will be based on the multivariate linear regression with adjustment for potential confounders. The difference for the change of BMI between the two groups will be estimated, and a corresponding 95 percent confidence interval will be calculated.

The sample size of the FIREHOUSE trial was estimated by the power analysis for the primary outcome of the change in BMI predicted between the start and end of the intervention, which was based on a two-sample test to compare the outcome between two groups under 1:1 randomization. According to the preliminary data, we assumed SD = 2 kg/m^2^ and the means of two groups “Usual Care” and “LoCalMed” to be 0 and −1 kg/m^2^, respectively. Furthermore, 6-month interventions with similar calorie targets and behavioral modification with exercise produce a 7–10 percent weight loss [37,38]. A total sample of 128 subjects (64 subjects in each arm) can achieve 80 percent power at α = 0.05. We will recruit 140 subjects accounting for potential loss of around 20 percent drop out.

The interim analysis plan will incorporate two interim looks and one final look, with all looks named as formal interim analysis, Table 5. This study will not be monitored for futility. The first look will be conducted at the completion of 6-month intervention or observation for 30 subjects in each group. This look will use 2-sided α < 0.001. The second look will be one formal interim look, which will be conducted at the completion of 50 subjects in each group with a 2-sided α = 0.007. The final analysis will take place at completion of all subjects in each group, with an O’Brien Fleming boundary for a 3-look design with 2-sided α = 0.033, Table 5 and Figure S1.

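### The two interim critical values in Table 5 are not O'Brien-Fleming bounds for looks at 30, 50 and 70 per group; they are stricter than the named design, with almost no effect on alpha or power

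*Protocol article*

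**What the plan says.** The subsection on sample size and interim analysis (Protocol article, section 2.2) sets out two interim looks and a final one:

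- Look 1: "The first look will be conducted at the completion of 6-month intervention or observation for 30 subjects in each group". Its level: "This look will use 2-sided α < 0.001".
- Look 2: "which will be conducted at the completion of 50 subjects in each group with a 2-sided α = 0.007".
- Final: at completion of all subjects, "with an O’Brien Fleming boundary for a 3-look design with 2-sided α = 0.033".

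Table 5 gives the same schedule as 30, 50 and 70 completers per group, with Z = 3.951, 2.686 and 2.129 and p = 0.000, 0.007 and 0.033. Its footnote calls the values "Interpolated boundaries with 3-look O’Brien Fleming stopping boundaries" and gives the design as "stopping boundaries 140 subjects randomized with 2-sided α = 0.036, power = 80" percent. The schedule, the boundary family and the overall alpha are therefore all stated, and the bounds can be checked from the article alone.

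**The concern.** An O'Brien-Fleming bound depends on the fraction of the final information available at each look. The stated looks are at 43% and 71% of the final sample. A first bound of 3.951 is what one would expect at about one third of the information, and 2.686 at about two thirds. These are the decision thresholds for the primary endpoint, the change in BMI. A monitoring body that applied the table would not be running the design the footnote names. For example, a look 2 result with Z between 2.574 and 2.686 would cross the spending-function boundary but not the printed one.

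**Working it through.** **Inputs.** From Table 5 and its footnote: 30, 50 and 70 per group; Z = 3.951, 2.686, 2.129; two-sided alpha 0.036; three looks; O'Brien-Fleming. From the sample size text: difference 1 kg/m², SD 2 kg/m², 1:1 allocation. Like Table 5, I take 70 per group as full information.

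**1. The table's p values follow from its Z values.** 2[1 − Φ(Z)] gives 0.00008, 0.0072 and 0.0333, which agree with the printed 0.000, 0.007 and 0.033.

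**2. Information fractions.** t = 30/70 = 0.429, 50/70 = 0.714, 70/70 = 1.

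**3. Bounds for that schedule at alpha 0.036.**

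- *Spending function.* Cumulative alpha spent is α(t) = 4[1 − Φ(z/√t)], where z is the upper α/4 = 0.009 point, 2.366. This gives 0.00060, 0.01025 and 0.036 at the three looks. The look 1 bound solves 2[1 − Φ(Z)] = 0.00060, so Z = 3.430. Recursive integration for the later looks gives 2.574 and 2.134.
- *Classical form.* Z = c/√t, with c chosen so that the total crossing probability is 0.036. This gives c = 2.144, and so 2.144/√0.429 = 3.275, 2.144/√0.714 = 2.537, and 2.144.

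| Look (per group) | Printed Z (p) | Spending Z (p) | Classical Z (p) |
|---|---|---|---|
| 30 | 3.951 (0.00008) | 3.430 (0.0006) | 3.275 (0.0011) |
| 50 | 2.686 (0.0072) | 2.574 (0.0100) | 2.537 (0.0112) |
| 70 | 2.129 (0.0333) | 2.134 (0.0328) | 2.144 (0.0320) |

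The look 1 gap is 0.52 to 0.68 in Z, which is not rounding. A different overall alpha does not rescue the table either. For the spending function to give 3.951 at 30/70, overall alpha would have to be about 0.014, and the later bounds would then be 2.98 and 2.48.

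**4. A schedule that nearly fits.** Spending bounds for equally spaced looks (t = 1/3, 2/3, 1):

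- alpha 0.035: 3.953, 2.687, 2.135
- alpha 0.0355: 3.943, 2.681, 2.130
- alpha 0.036: 3.934, 2.674, 2.124

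All are within 0.02 of the printed values, but none matches all three.

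**5. Overall alpha of the printed bounds.** The total probability of crossing under no difference is 0.0355 at equal thirds, which rounds to the footnote's 0.036. At 30/50/70 it is 0.0351.

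**6. Behaviour under the design effect.** The mean of Z with n per group is 1/(2√(2/n)), which is 1.936, 2.500 and 2.958 at n = 30, 50 and 70.

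- Look 1 crossing, printed: 1 − Φ(3.951 − 1.936) = 2.2%. Spending: 1 − Φ(3.430 − 1.936) = 6.8%. Classical: 1 − Φ(3.275 − 1.936) = 9.0%.
- Crossing by look 2 (recursive integration): 42.6% printed, 47.2% spending, 48.8% classical.
- Overall power: 79.9% printed, 80.0% spending, 79.8% classical.
- Observed BMI difference needed at look 1, Z × 2√(2/30): 2.04 kg/m² printed, against 1.77 (spending) and 1.69 (classical).

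**The case against.** The best defence is that stricter interim bounds are still valid bounds. Type I error is not inflated, power is unchanged to within 0.1 percentage point, and the final threshold is right to within 0.005 of the spending-function value. The text attaches the O'Brien-Fleming name only to the final analysis and gives plain nominal levels for the two interim looks. The footnote says the values are interpolated without explaining how, and Figure S1 is not at hand. All of this stands as a limit on the consequence. It does not remove the inconsistency, because the footnote names O'Brien-Fleming for all three looks and states no other function, and neither standard form gives the printed interim values for this schedule.

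A reader might also infer three stronger points that the documents do not support:

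- *That bounds for equal thirds were copied beside the wrong counts.* This is likely, but it is a near match only; no single alpha tried reproduces all three printed values.
- *That every nominal level in the text is wrong.* With spending bounds at 0.036, the levels below 0.001 and of 0.033 still hold. Only the 0.007 changes.
- *That the 20 percent drop-out allowance makes the fixed counts an error.* Table 5 sets the last look at 70 completers, and how bounds are re-evaluated at the actual counts is ordinary content of an analysis plan that is not shown.

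**Conclusion.** The point holds as an inconsistency between the printed interim thresholds and the design and schedule stated with them. At two-sided alpha 0.036 the look 1 value should be 3.430 or 3.275, not 3.951, and the look 2 value 2.574 or 2.537, not 2.686, depending on which O'Brien-Fleming form is meant.

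It would be wrong to conclude that the trial's inference is at risk. Overall alpha falls short of the stated figure by 0.036 − 0.0351 = 0.0009, in the safe direction. The practical cost is a lower chance of stopping early for benefit: 4.6 to 6.8 percentage points lower at look 1, and 4.6 to 6.2 points lower by look 2.

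This rests on 70 completers per group as full information, the stated alpha of 0.036, and the plan's own difference of 1 and SD of 2 kg/m².

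**What to change.** **If no unblinded interim result has been seen:** recompute Table 5 for fractions 0.429, 0.714 and 1, and name the boundary form. With the spending function at 0.036 the row values become Z = 3.430, 2.574 and 2.134, with p = 0.0006, 0.010 and 0.033. In the interim analysis text, change the look 2 level from 0.007 to 0.010 and leave the other two as they are. If the classical form is chosen instead, the look 1 level of 0.0011 no longer meets the statement that it is below 0.001, so that wording would need changing too, as would the look 2 and final levels (0.011 and 0.032).

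**If a look has already taken place:** keep the stricter printed bounds. Correct the footnote to say that they are not O'Brien-Fleming bounds at these looks and that they give an overall two-sided alpha of about 0.035. This option matters because section 2.3 shows that the un-blinded trial was already under way, and the article does not say whether look 1 had occurred. Loosening thresholds with results in view would not be acceptable.

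**Cost:** one table and one level in the text for the spending-function version, or one footnote for the alternative. No extra participants or procedures are needed. If the bounds are recomputed, crossing early becomes slightly more likely.

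### The sample size (alpha 0.05, 128 subjects, no looks) and the Table 5 decision rule (overall alpha 0.036, 140 subjects) are two unreconciled designs, and the printed bounds do not fit the stated looks

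*Protocol article*

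**What the plan says.** Section 2.2 of the protocol article, under Sample Size and Interim Analysis, describes a power calculation "based on a two-sample test to compare the outcome between two groups under 1:1 randomization". For the SD it says "we assumed SD = 2 kg/m^2", and it takes "the means of two groups “Usual Care” and “LoCalMed” to be 0 and −1 kg/m^2^, respectively". The result is "A total sample of 128 subjects (64 subjects in each arm) can achieve 80 percent power at α = 0.05". Recruitment is then raised: "We will recruit 140 subjects accounting for potential loss of around 20 percent drop out".

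The same section adds two interim looks, at 30 and 50 completers per group, and a final look, with nominal two-sided levels below 0.001, 0.007 and, at the end, a "boundary for a 3-look design with 2-sided α = 0.033". There is no futility rule. Table 5 prints critical values 3.951, 2.686 and 2.129 at 30, 50 and 70 per group. Its footnote calls them interpolated three-look O'Brien-Fleming boundaries and gives "stopping boundaries 140 subjects randomized with 2-sided α = 0.036, power = 80" percent.

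For the primary BMI difference, "a corresponding 95 percent confidence interval will be calculated".

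**The concern.** The article prints two overall significance levels for one primary comparison, 0.05 and 0.036, and neither place refers to the other. The sample size paragraph makes no allowance for the looks, and the table does not use the sample size paragraph's alpha or its number of subjects. The 140 subjects also serve two purposes: in the text they are the allowance for drop-out, while in Table 5 they are all completers at the final look.

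Two things are at stake. First, the 80% quoted for 128 subjects does not describe the test that will decide the trial. Second, a final p between 0.033 and 0.05 would pass the alpha in the sample size paragraph and fail Table 5, and that choice should not remain open until the data are seen. Separately, critical values computed for a different look schedule cannot be taken as the O'Brien-Fleming rule for this one.

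**Working it through.** **Inputs** (Sample Size and Interim Analysis; Table 5): difference 1 kg/m², SD 2 kg/m², 1:1 allocation, looks at 30 and 50 per group and at the end, bounds 3.951/2.686/2.129, 140 recruited, about 20% drop-out.

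**1. The plan's 128.** The normal formula gives n per arm = 2(1.960 + 0.842)² × 2² / 1² = 62.8, so 63. The two-sample t-test gives 79.5% power at 63 per arm and 80.15% at 64. The stated 64 per arm is reproduced for a single two-sided test at 0.05.

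**2. Overall alpha of the printed bounds.** The nominal p values of 3.951, 2.686 and 2.129 are 0.00008, 0.0072 and 0.0333, which agree with the text. Integrating the joint distribution of the three statistics under no effect gives a total of 0.0351 at fractions 30/70, 50/70 and 1, and 0.0355 at 1/3, 2/3 and 1. The second value rounds to the footnote's 0.036.

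**3. Do the bounds fit the looks?** The stated looks are at 30/70 = 43%, 50/70 = 71% and 100%. The Lan-DeMets O'Brien-Fleming spending used is α(t) = 4[1 − Φ(z(1−α/4)/√t)].

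| Looks | Overall alpha | Method | Bounds |
|---|---|---|---|
| Table 5, as printed | 0.036 | not stated further | 3.951 / 2.686 / 2.129 |
| Equal thirds | 0.0355 | Lan-DeMets | 3.943 / 2.681 / 2.130 |
| 30/50/70 | 0.036 | Lan-DeMets | 3.430 / 2.574 / 2.134 |
| 30/50/70 | 0.036 | classic O'Brien-Fleming | 3.275 / 2.537 / 2.144 |
| 30/50/70 | 0.05 | Lan-DeMets | 3.231 / 2.418 / 2.004 |

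The printed row lies close to the equal-thirds row. Neither method at 30/50/70 returns it.

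**4. Power under each rule.** The expected final Z is 1 / (2√(2/n)), which is 2.958 at n = 70, 2.828 at 64 and 2.646 at 56. The last n is 140 × 0.80 = 112 completers. Looks are kept at 30 and 50 per group, and the Lan-DeMets bounds are recomputed for each final n.

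| Completers per arm | Table 5 bounds | Lan-DeMets, overall 0.05 |
|---|---|---|
| 70 | 79.9% | 83.5% |
| 64 | 76.0% | 79.9% |
| 56 | 69.8% | 74.2% |

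Table 5's own 80% at 140 is therefore reproduced, but only if nobody drops out. The gap between the columns is 3.6 to 4.4 points.

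**5. The ambiguous zone.** At the planned effect with 70 per arm, replacing the final bound 2.129 by 1.96 raises the rejection probability from 79.9% to 84.2%. The trial would therefore end with a final p between 0.033 and 0.05 about 4.3% of the time.

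**The case against.** The strongest reply is that neither stated power figure is miscalculated. A reader might infer that 80% at 128 is simply wrong. The documents do not support that: it is correct for the single test at 0.05 to which it is attached, and it stays at 79.9% with O'Brien-Fleming looks at overall 0.05. Table 5 attaches its 80% to 140 subjects, and that also holds. The value 0.036 may be deliberate.

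A reader might also infer that the misplaced looks inflate false positives. They do not, since 0.0351 is below both 0.036 and 0.05. The 0.033 in the text and the 0.036 in the footnote are not in conflict either, because one is the final nominal level and the other the overall level.

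The 95% confidence interval invites another strong reading. If success were read from it, total type I error would be 0.0512. But the article presents the interval as an estimate and nowhere makes it the test, so that figure describes a misuse the plan does not prescribe. Nor does the article say that an interim look has taken place, so there is no basis for claiming that alpha has been spent. Finally, the trial calls itself exploratory and the error is conservative, which limits the harm.

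All of this stands. It leaves untouched the two unexplained alphas, a power figure for 128 that does not apply to the printed rule, and bounds that belong to another look schedule. The footnote's description of the boundaries as interpolated does not say how they would follow from 30/50/70.

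**Conclusion.** The point holds as a failure to reconcile two calculations, each sound on its own inputs. Under the bounds that decide the trial, power is 76.0% at the 64 per arm the plan calls sufficient. It reaches 79.9% only with no drop-out and falls to 69.8% with the plan's own 20%. The price relative to spending 0.05 at the stated looks is about 4 points of power, with no gain that the article explains, plus an undecided outcome for a final p between 0.033 and 0.05. Type I error is controlled.

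These figures assume the plan's difference of 1 and SD of 2, normally distributed test statistics, information proportional to completers, and interim looks held at 30 and 50 per group. The fit to equal thirds is an inference from the numbers; the article does not state how the bounds were obtained.

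Part of the drop to 69.8% comes from recruitment rather than alpha. Covering 20% loss from 128 needs 128/0.80 = 160, while 140 covers (140 − 128)/140 = 8.6%. That is a related but separate matter.

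**What to change.** State one overall two-sided alpha and use it in both the sample size paragraph and Table 5. The article does not show which was intended, so the choice is the sponsor's. Recompute the bounds by alpha spending at the actual completer fraction at each look, with the final bound taken from the real number of completers. Restate power for that alpha and for the number expected to complete.

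- If 0.05 is chosen, the bounds at 30/50/70 are 3.231/2.418/2.004 (nominal p 0.0012, 0.0156, 0.0451), and power is 83.5% at 70, 79.9% at 64 and 74.2% at 56 per arm.
- If 0.036 is chosen, give the reason. The bounds at 30/50/70 are 3.430/2.574/2.134. If the Table 5 values are kept instead, restate power as 76.0% at 64 and 69.8% at 56 per arm.

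As a minor point, say that significance is judged by the final boundary and not by the 95% interval. Alternatively, report the interval at the matching level, which is 96.7% for Z 2.129 and 2.129/1.96 = 1.086 times as wide, about 9% more.

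The cost is one recomputed table and a few edited sentences, with no additional patients.
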